## Abstract

**Background:**

Early phase research suggests that physiotherapy paired with use of robotic walking aids provides a novel opportunity for children with severe mobility challenges to experience active walking. The Trexo Plus is a pediatric lower limb exoskeleton mounted on a wheeled walker frame, and is adjustable to fit a child’s positional and gait requirements. It guides and powers the child’s leg movements in a way that is individualized to their movement potential and upright support needs, and can provide progressive challenges for walking within a physiotherapy-based motor learning treatment paradigm.

**Methods:**

This protocol outlines a single group mixed-methods study that assesses the feasibility of physiotherapy-assisted overground Trexo use in school and outpatient settings during a 6-week physiotherapy block. Children ages 3–6 years (*n* = 10; cerebral palsy or related disorder, Gross Motor Function Classification System level IV) will be recruited by circle of care invitations to participate. Study indicators/outcomes will focus on evaluation of: (i) clinical feasibility, safety, and acceptability of intervention; (ii) pre-post intervention motor/functional outcomes; (iii) pre-post intervention brain structure characterization and resting state brain connectivity; (iv) muscle activity characterization during Trexo-assisted gait and natural assisted gait; (v) heart rate during Trexo-assisted gait and natural assisted gait; and (vi) user experience and perceptions of physiotherapists, children, and parents.

**Discussion:**

This will be the first study to investigate feasibility indicators, outcomes, and experiences of Trexo-based physiotherapy in a school and outpatient context with children who have mobility challenges. It will explore the possibility of experience-dependent neuroplasticity in the context of gait rehabilitation, as well as associated functional and muscular outcomes. Finally, the study will address important questions about clinical utility and future adoption of the device from the physiotherapists’ perspective, comfort and engagement from the children’s perspective, and the impressions of parents about the value of introducing this technology as an early intervention.

**Clinical trial registration:**

https://clinicaltrials.gov, identifier NCT05463211

## 1 Introduction

While wheelchairs are essential for supporting mobility and participation in the daily activities of individuals who have severe motor impairments (Gibson et al., 2012), they do not offer supported upright positioning of the body. Many individuals with limited mobility use a combination of assistive devices for different intentions or circumstances, such as wheelchairs, standing frames, and supported walkers (Moen and Østensjø, 2023). Walking (or assisted standing) confers a multitude of health benefits including improved bone health (Kim et al., 2017), respiration (Lee and Kim, 2014), circulation (Eng et al., 2001), urination (Houle et al., 1998; Walter et al., 1999), bowel function (Walter et al., 1999), joint range of motion (Paleg et al., 2013), sleep (Eng et al., 2001), as well as psychosocial (McKeever et al., 2013; Livingstone and Paleg, 2023) and mental health benefits (Kenyon et al., 2021). Growing recognition across rehabilitation sectors about the possibility of technology to facilitate enhanced upright mobility and independence has stimulated the engineering advancement of assistive gait devices from simple wheeled walkers (Tao et al., 2020), to supported stepping devices (Livingstone and Paleg, 2023), to non-robotic mechanically facilitated walkers (Wright and Jutai, 2006; Paleg and Livingstone, 2015), to treadmill mounted (tethered) gait trainers (Cherni and Ziane, 2022), and most recently to powered exoskeletons that move overground (Owens et al., 2020).

Overground lower-limb powered exoskeletons afford earth vertical weight-bearing positioning that is coupled with augmented mobility (De Luca et al., 2019), giving novel upright movement opportunities when foundational gross motor skills (e.g., learning to walk) are delayed or when disease or injury has resulted in loss of independent walking abilities (Hunt, 2021). These exoskeletons can be used in conjunction with other gait aids such as wheeled walkers, or tethered on a treadmill (Kim et al., 2021) to fit the individual’s support needs. They can also be built as freestanding robotically guided mobile walking frames (De Luca et al., 2019; Sarajchi et al., 2021). The added value of exoskeleton use within gait-based physiotherapy sessions is that they provide: the option of hands-free body weight support (thereby freeing the arms/hands for other activities), sensors that respond to biological feedback, natural joint movements and activation of weak or spastic muscles by modulating forces on body segments, normalization of the gait cycle by standardizing step length and range of motion, reduced cost of walking to allow meaningful periods of exercise during intervention sessions, quantified session progress to provide real-time feedback, and supported use of motor learning protocols (intensity, repetition, variability, and task-specificity) to optimize gait training (Molteni et al., 2018; De Luca et al., 2019).

Increased clinical adoption of mobile exoskeletons such as the Angel-legs (Angel Robotics Co., Ltd., Seoul, Korea), ReWalk (ReWalk Robotics Inc., Marlborough, MA, USA), and Ekso (Ekso Bionics, Richmond, CA, USA) has occurred over the last decade in adult rehabilitation, and there is an emerging body of evidence of the physical and health benefits of exoskeleton use by adults with neuromotor conditions (Louie and Eng, 2016; Bruni et al., 2018; Rojek et al., 2020; Karunakaran et al., 2021; Rodríguez-Fernández et al., 2021). However, development and access to smaller sized exoskeletons for pediatric populations, and associated clinical experience with using them, currently lags far behind that of adults (Fosch-Villaronga et al., 2020). As a result, there is limited knowledge on the neurological and neuromuscular effects of exoskeleton use in children, as well as the training considerations and user perspectives that are essential to facilitate best practice use. The majority of research to date on robotic walkers in pediatrics has been with treadmill-based tethered models such as the Lokomat robotic gait trainer (Hocoma AG, Volketswil, Switzerland) (Aurich-Schuler et al., 2015; Cumplido et al., 2021; Kim et al., 2021; Cherni and Ziane, 2022). While tethered exoskeletons offer weightbearing and gait training benefits (Kim et al., 2021), they do not provide the functional and participation opportunities obtained from the added experience of moving overground with mobile exoskeletons like Ekso, Trexo pediatric frame-mounted exoskeleton (Trexo Robotics, 2022), or similar devices.

The Trexo Plus (hereafter referred to as the Trexo), designed specifically for use with children with motor impairments, has been commercially available since 2017. Thus far it has been investigated in the context of home use with children’s caregivers operating the device after orientation provided by the Trexo team (Diot et al., 2021, 2023). Benefits in the areas of sleep quality, bowel function, postural function, and positive affect associated with Trexo use have been documented (Diot et al., 2023). At the time of writing, Trexo use is being evaluated in a follow-up crossover feasibility RCT (4-week Trexo home program [prescribed/taught by a PT and facilitated by the child’s caregiver 4–5 times/week] compared with a 4-week identical frequency functional therapy program [prescribed/taught by a PT and facilitated by the child’s caregiver]) (McCormick et al., 2023).

There are no published studies to date that focus on integration of the Trexo into clinical settings, specifically physiotherapist-led therapy sessions. There is evidence though of adoption-related challenges for rehabilitation teams using exoskeletons in adult rehabilitation, such as extensive knowledge requirements and hands-on skill demands to handle the operation of these advanced new technologies for competent goal-based therapeutic use, while ensuring patient safety and comfort (Read et al., 2020). There is also the need for strong teamwork within a facility to collaboratively develop therapy protocols for each patient that will optimize outcomes (Gilardi et al., 2020).

Paradigmatic shifts in thinking about possible walking-based outcomes for minimally ambulatory children (van Hedel et al., 2016; Livingstone and Paleg, 2023) are occurring in tandem with assistive device developments. For example, typical physiotherapy and occupational therapy goals for children with cerebral palsy (CP) who are minimally ambulatory or non-ambulatory (i.e., Gross Motor Function Classification System [GMFCS] levels IV and V respectively) have traditionally focused on achieving their highest degree of independence within the context of their physical constraints (Goswami et al., 2021). The recent introduction of overground robotic devices (such as the Trexo) has been encouraging a transition in practice toward providing more active focus on upright assisted walking within home and community environments, especially in children’s younger years, using a physiotherapy intervention approach that is based on principles of motor learning and neuroplasticity. However, from a best practice perspective, there is an urgent responsibility to gather clinical evidence both on intervention processes and associated outcomes before making them a part of regular clinical care (Phelan et al., 2015).

The primary aim of this study is to investigate the feasibility, user perspectives, and body-wide outcomes associated with institutionally based overground exoskeleton gait training in children 3–6 years of age with a functional presentation of GMFCS level IV. The Trexo will be the overground lower limb exoskeleton used. It is listed as a Class I medical device by Health Canada and Class II medical device by the FDA.

The study aims will be completed through a study protocol with the following objectives:

i)Assess aspects of clinical feasibility, safety, and acceptability of Trexo gait training within an outpatient center and schoolii)Capture the Trexo user experience of children and physiotherapists during exoskeleton gait training, as well as physiotherapists’ and parents’ perspectives of outcomes associated with useiii)Assess motor and functional outcomes pre/post Trexo gait training (including any carryover effects)iv)Examine brain anatomy and brain connectivity pre/post Trexo gait trainingv)Evaluate muscle activations, particularly indicating muscle fatigue, during Trexo gait training (compare with muscle activations during use of regular assistive mobility devices)vi)Capture heart rate and heart rate variability during Trexo gait training (compare with heart rate during use of regular assistive mobility devices).

## 2 Methods and analysis

### 2.1 Study design

This mixed methods feasibility study protocol [phase IIa; Orbit Model (Czajkowski et al., 2015) uses an **O_0_ X O_1_ O_2_** design (Figure 1), with participants (*n* = 10) acting as their own controls (within a longitudinal intervention consisting of O_0_, O_1_, and O_2_ = study assessment phases, and X = physiotherapy intervention with the Trexo]. The protocol follows Standard Protocol Items: Recommendations for Interventional Trials (SPIRIT Checklist; Chan et al., 2013a,b). All study team members’ roles are outlined in Table 1.

**FIGURE 1 F1:**
[figure not shown]
Flow chart of study visits and timeline, reflecting O_0_ X O_1_ O_2_ design.

**TABLE 1 T1:** Research team member designations and corresponding roles in the study.

Designation	Role
Principal investigators	Responsible for study oversight and adverse event management.
Study researchers	Non-PT team members that are responsible for coordinating recruitment, scheduling, non-PT data collection, and data analysis.
Study physician	Center-affiliated pediatrician that helps with diagnostic expertise, recruitment, eligibility, and adverse event management.
Treating PTs/PTAs	Physiotherapy team members that are Trexo-trained and complete the 12 Trexo (twice weekly) intervention sessions.
PT assessors	Independent PTs (different from treating PTs) that complete the physical screening and motor/functional assessments.
Study interviewer	Independent team member that hosts all Zoom-based interviews.
MRI technician	Centre-affiliated technician that operates MRI scanner.

During ‘**O’ phases (pre/post intervention)**, participants will do their usual physiotherapy regimen (with their usual assistive device, where applicable) and associated home program, and will undergo the set of study assessments (gross motor/functional assessments and neuroimaging) in this approximately 2–3-week period pre- and post-Trexo use (Phase X). One-month post O_1_, participants will have one final motor/functional assessment and neuroimaging visit (O_2_). They will continue with their usual physiotherapy regimen during the month between O_1_ and O_2_.

**Intervention ‘X’ phase** will consist of the Trexo physiotherapy block: physiotherapy sessions twice weekly (30-min sessions excluding initial set-up time) for 6 weeks provided by a study-trained PT/Physiotherapist Assistant (PTA) team within a goal-based training program that is grounded in motor learning principles. Trexo physiotherapy will be integrated within a school-based program for half of the study cohort (*n* = 5), and within an outpatient program for the other half (*n* = 5). Each child will receive 1–2 acclimatization/fitting sessions in the Trexo before starting physiotherapy sessions. Walking tests and muscle recordings at the start and end of this phase will be done in the Trexo and in the child’s usual non-robotic wheeled walker (if they use one) for comparison and for assessment of potential carryover effects from Trexo use to their wheeled walker.

Independent PT assessors (different from the intervention PTs) will perform motor/functional assessments, with the same assessor assigned to a child for each assessment. They will be blinded to the results of their previous assessment(s). Treating Trexo PTs and PTAs may choose to share their experience of using the Trexo as an intervention via optional qualitative interviews pertaining to: (i) their Trexo training/learning process, and (ii) the treatment process specific to each of the children who is assigned to them. Parents may choose to share their expectations and impressions of the Trexo treatment block via optional qualitative interviews pertaining to: (i) baseline study expectations, and (ii) post-intervention impressions and any associated outcomes of their child’s use.

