#### 2.6.1 Gross motor skills

The *Gross Motor Function Measure* (GMFM-88; Russell et al., 2000) will be administered by an independent PT assessor during the motor/functional assessment at baseline and immediately post-intervention. It will also be used 1-month post-intervention to gauge maintenance/progression of any functional gains. PT assessors will be trained on the GMFM-88 and all other PT assessment measures by the study’s co-principal investigator prior to their first study assessment. All PTs will already have extensive clinical experience administering the GMFM with children with CP, and variable experience with the other measures. The full 88-item version of the GMFM will be used as it more comprehensively captures a range of abilities in its lowest dimensions (Lie/Roll and Sit) than the abbreviated GMFM-66. This will be important as better trunk and head control are anticipated to be goals and potential outcomes associated with Trexo use in children in GMFCS Level IV. The GMFM-88 testing will be captured on video to enable post-assessment review by PTs. Pre/post change scores will be calculated with descriptive statistics representing results of the group. The GMFM has excellent test-retest reliability (Bjornson et al., 1998), and responsiveness to change (Vos-Vromans et al., 2005).

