#### 2.6.2 Functional priority goals

The PT assessor will guide the attending parent(s) through the *Canadian Occupational Performance Measure* (COPM; Law et al., 1990) during the baseline functional assessment visit to set priority outcome goals for their child. These 3–4 goals will be guided from a menu prepared by the investigators of walking-based or other functional outcomes that may arise from Trexo use. These goals can relate to the child’s abilities in home, school, or community environments. The parent(s) will use the COPM’s 10-point response scales to rate the importance of each goal, as well as satisfaction and performance of each at baseline. COPM goals will be rated by the parent(s) again at the post-intervention assessment, as well as the 1-month post intervention assessment. All efforts will be made to have the same parent attend each assessment to maintain consistency. The parent(s) and assessor will be blinded to previous COPM scores. Pre/post mean change scores will be calculated for each child. The COPM has been adapted for use with children and has demonstrated strong internal consistency, construct validity, and responsiveness to change (Cusick et al., 2007).

*Goal Attainment Scaling* (GAS) goals and achievement levels will be set by the treating PTs, and will be Trexo-directed or regular walker-associated. GAS will serve as an individualized measure of change for each child and will link to the parent-chosen COPM goals to allow evaluation of the targeted subcomponents of COPM’s higher level functional priority goals (King et al., 2000; Ostensjo et al., 2008). These two or three goals will be set by the 3*^rd^* physiotherapy session, allowing the PT team to first form a realistic idea of the child’s functional abilities and potential areas of improvement. GAS outcomes will be scored per goal by the child’s treating PT upon completion of the child’s last physiotherapy session, and a summary T-score will also be calculated. GAS is commonly used with children with CP who use walkers, and has demonstrated strong internal consistency, construct validity, and responsiveness to change (Paleg and Livingstone, 2016).

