#### 2.7.2 Postural control assessments

Two postural assessments will be administered by the physiotherapist assessor, and scored from video that will be captured during the assessment by a research assistant using a standardized camera angle protocol.

The *Posture and Postural Ability Scale* (PPAS; Rodby-Bousquet et al., 2016) is a validated measure for children with CP in GMFCS levels II to V. It will rate the symmetry and alignment of the child’s head, trunk, pelvis, legs, arms, and weight distribution in frontal and sagittal planes. The child will be guided into prone, supine, sitting and supported standing positions (30 s in each) by the assessor. Scoring will be done from the video of the assessment.

The *Level of Sitting Scale* (LSS) (Fife et al., 1991; Field and Roxborough, 2011) is designed for children who are wheelchair users and require some degree of external support (GMFCS IV and V). The LSS will classify a child’s sitting ability without feet supported. It will serve as both a descriptive measure of children enrolled in the study and also an outcome measure in tandem with the PPAS. It will be scored from the PPAS video.

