#### 2.7.4 Gait assessments

Functional gait will be assessed via a *1-minute walk test* (1MWT) (Hassani et al., 2014) and the *Directional Mobility Assessment* (DMA) (Wright and Jutai, 2006; Livingstone and Paleg, 2016), done in the child’s regular walking device (if they use one) and the Trexo walker. The 1MWT will measure the distance walked down a straight wide hallway within 60 s with the Trexo and with the child’s regular walker, with support from the child’s PT/PTA team as needed for steering (Trexo and regular walker) and facilitating steps (regular walker). The DMA incorporates a functional walking course: straight walking, turns, obstacles, narrow path, and backing up.

These walking tasks will be administered by the child’s treating PT/PTA simultaneously during MMG/heart rate monitoring (facilitated by study researchers). Involvement of the PT/PTA in this testing is essential as they are Trexo-trained and aware of the child’s functional abilities and safety considerations. A video recording will be made of these walking tests to permit their rating by an independent PT assessor to maintain independence of scoring from the clinical team.

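### GMFM-88 and the video-rated tests are not masked to time point in a single-group before-after study, although the recordings would allow it; GAS is set and scored by the treating therapist

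*Protocol article*

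**What the plan says.** The design is one group with children "acting as their own controls" (Section 2.1). PT assessors who do not treat the children carry out the motor and functional assessments. On assignment and masking, the section says: "with the same assessor assigned to a child for each assessment. They will be blinded to the results of their previous assessment(s".

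For the individual measures:

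- **GMFM-88** (Section 2.6.1) is administered by the PT assessor at baseline, after the block and one month later. The video has a limited stated use: "The GMFM-88 testing will be captured on video to enable post-assessment review by PTs".
- **PPAS and LSS** (Section 2.7.2) are rated from recordings. For the PPAS: "Scoring will be done from the video of the assessment". The LSS uses the same film.
- **1MWT and DMA** (Section 2.7.4) are run by the treating team but rated elsewhere: "A video recording will be made of these walking tests to permit their rating by an independent PT assessor". The stated reason is to keep scoring separate from the treating team.
- **GAS** (Section 2.6.2; primary in Table 2): "goals and achievement levels will be set by the treating PTs". The child's treating PT also scores attainment after the last session.
- **COPM** (Section 2.6.2) is rated by the parent. Parent and assessor do not see earlier scores.

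Section 2.11.1 plans paired t-tests or non-parametric equivalents, baseline against post-intervention, for GMFM-88 and COPM and then for each secondary outcome.

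**The concern.** With no comparison group, the order of the visits is the treatment contrast. A rater who knows the visit knows which score is expected to be higher. Hiding earlier scores reduces anchoring but leaves this expectation in place. Any generosity at the later visit adds to the mean change, and no control arm has the same bias to subtract.

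This matters most for the GMFM-88, which is a co-primary measure, is scored by an observer and is tested for change. It is also already filmed, so masked scoring is possible without another visit. GAS raises a related but separate issue: the same therapist sets the goals, delivers the treatment and judges success.

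**Working it through.** **Step 1. Who scores, and what masking is stated.**

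| Measure | Scored by | Video mentioned | Masking stated |
|---|---|---|---|
| GMFM-88 | child's PT assessor | yes, for later review | own earlier results |
| PPAS, LSS | from video, after assessment by the PT assessor | yes | general assessor rule only; nothing on time point |
| 1MWT, DMA | independent PT assessor, from video | yes | nothing on time point |
| ROM, Tardieu | PT assessor | no | own earlier results |
| COPM | parent, with PT assessor | no | earlier scores |
| GAS | treating PT | not for scoring | none |
| MRI, MMG | instrument | not applicable | not applicable |

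Masking to time point is stated for no measure.

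**Step 2. Does the child's assessor know the visit?** The article does not say so, but its schedule implies it. At baseline the same assessor guides the parent in choosing COPM goals (Section 2.6.2) and completes the MACS (Section 2.8.1). Neither task is repeated; later visits only re-rate the goals. Heart rate is recorded at the post-intervention functional assessment and not at baseline (Section 2.7.5). The inference is strong for anything scored by the assessor who ran the visit. It does not carry over to a separate rater who sees only a clip, as may be the case for 1MWT and DMA.

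**Step 3. What a scoring shift would do to the paired test.** The plan has no figure to reproduce: Section 2.2.4 justifies n = 10 descriptively, with no alpha, power or SD. Assumptions: two-sided alpha of 0.05, no true change, and a systematic shift of b SDs of the change score at the later visit. The test statistic then follows a non-central t distribution with n − 1 degrees of freedom and non-centrality λ = b√n, and

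P(reject) = P(T > t_crit) + P(T < −t_crit).

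For n = 10, √10 = 3.162 and t_crit(9) = 2.262. The retention target of at least 90% allows n = 0.9 × 10 = 9, where √9 = 3 and t_crit(8) = 2.306.

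| b (assumed) | λ, n = 10 | P(reject), n = 10 | λ, n = 9 | P(reject), n = 9 |
|---|---|---|---|---|
| 0 | 0 | 5.0% | 0 | 5.0% |
| 0.2 | 0.632 | 8.8% | 0.6 | 8.3% |
| 0.3 | 0.949 | 13.6% | 0.9 | 12.5% |
| 0.5 | 1.581 | 29.3% | 1.5 | 26.3% |

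Nearly all the excess falls on the favourable side. At n = 10 and b = 0.2, favourable false positives are 8.2%, against a nominal 2.5%.

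**Step 4. Where these figures apply.** They describe observer-scored measures given a paired test, chiefly the GMFM-88. They do not describe GAS, which is scored once as attainment with a T-score and is not named for paired testing in Section 2.11.1.

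**The case against.** The other side has real weight.

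- **Safeguards exist.** Assessors are separate from treatment, one assessor follows each child, earlier scores are hidden, and walking tests go to an independent rater. This stands, but none of it hides the visit from the GMFM-88 assessor.
- **The bias is assumed.** Neither the shift nor the alpha comes from the documents. This stands: the figures show what a shift would do, not that one exists.
- **It is a feasibility study.** The sample supports description, and Section 2.6.1 describes GMFM-88 change descriptively. This lowers the weight of the point. It does not remove it, because Section 2.11.1 still tests change and a descriptive mean change carries the same bias.
- **Silence in an article is not a defect.** Clip order and labelling may be set in the full protocol. For PPAS, LSS, 1MWT and DMA this stands, and there the point is only to state the masking. For the GMFM-88 the article does state a masking rule, and that rule stops at earlier results.
- **Masked video scoring is incomplete.** The assessor who runs the GMFM-88 still knows the visit and can encourage the child differently. This stands.

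A reader might infer that every outcome is scored by someone who knows the visit, so that every before-after difference is biased. The documents do not support that. MRI and MMG are instrument-based, the 1MWT is a measured distance, COPM is the parent's own rating, and nothing shows that the 1MWT and DMA video rater knows the date. A reader might also infer that the recordings would solve the GAS problem. No video is planned for GAS scoring, and the one filmed therapy session is for rating motor learning strategies.

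**Conclusion.** The point holds in limited form. The GMFM-88 is scored by the same assessor at each visit, who is masked to earlier scores but in practice not to time point. PPAS, LSS, 1MWT and DMA ratings have no stated masking to time point. In an uncontrolled before-after design this lets expectation favour the later scores. If the shift were 0.2 to 0.5 SD of the change score, a nominal 5% test at n = 10 would reject in about 9% to 29% of trials with no true change (8% to 26% at n = 9). The result rests on an assumed shift, an assumed two-sided alpha of 0.05 and a paired t-test; the true size is unknown.

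GAS is rated by the treating therapist and should be read that way. The article contains no contradiction here. This is a design improvement that should be made because the recordings are already planned.

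**What to change.** 1. **PPAS, LSS and DMA.** After each child's last visit, score the planned recordings in random order with dates removed. These ratings are already made from video, so mainly labelling, order and timing change. The 1MWT, a distance, gains little.
2. **GMFM-88.** Have a PT assessor already on the team who did not assess that child score the recordings in the same way, with one rater for all of a child's clips so that within-child consistency is kept. Table 1 lists PT assessors in the plural, so this assumes that a second one is available. Use the masked score in the analysis, or at least report it beside the live score. Decide beforehand how to treat items that cannot be seen on film.
3. **GAS.** Label it as an unmasked rating by the treating therapist and interpret it accordingly. Add independent scoring from the end-of-block walking video only where the goal is visible there.
4. **State the limits.** An unmasked assessor still administers the GMFM-88. The heart-rate strap, worn only post-intervention, may reveal the visit on film. COPM, ROM and Tardieu remain unmasked.

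The cost is GMFM-88 scoring time, at most 10 children × 3 visits = 30 recordings (20 for the baseline against post-intervention comparison alone), and scores that become available later. No new visits or tests are needed.
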